## Abstract

**Background:**

Various randomized trials have demonstrated that postmastectomy radiotherapy (RT) to the chest wall and comprehensive regional nodal areas improves survival in patients with axillary node-positive breast cancer. Controversy exists as to whether the internal mammary node (IMN) region is an essential component of regional nodal irradiation. Available data on the survival benefit of IMN irradiation (IMNI) are conflicting. The patient populations enrolled in previous studies were heterogeneous and most studies were conducted before modern systemic treatment and three-dimensional (3D) radiotherapy (RT) techniques were introduced. This study aims to assess the efficacy and safety of IMNI in the context of modern systemic treatment and computed tomography (CT)-based RT planning techniques.

**Methods:**

POTENTIAL is a prospective, multicenter, open-label, parallel, phase III, randomized controlled trial investigating whether IMNI improves disease-free survival (DFS) in high-risk breast cancer with positive axillary nodes (pN+) after mastectomy. A total of 1800 patients will be randomly assigned in a 1:1 ratio to receive IMNI or not. All patients are required to receive ≥ six cycles of anthracycline and/or taxane-based chemotherapy. Randomization will be stratified by institution, tumor location (medial/central vs. other quadrants), the number of positive axillary nodes (1–3 vs. 4–9 vs. ≥10), and neoadjuvant chemotherapy (yes vs. no). Treatment will be delivered with CT-based 3D RT techniques, including 3D conformal RT, intensity-modulated RT, or volumetric modulated arc therapy. The prescribed dose is 50 Gy in 25 fractions or 43.5 Gy in 15 fractions. Tiered RT quality assurance is required. After RT, patients will be followed up at regular intervals. Oncological and toxilogical outcomes, especially cardiac toxicities, will be assessed.

**Discussion:**

This trial design is intended to overcome the limitations of previous prospective studies by recruiting patients with pN+ breast cancer, using DFS as the primary endpoint, and prospectively assessing cardiac toxicities and requiring RT quality assurance. The results of this study will provide high-level evidence for elective IMNI in patients with breast cancer after mastectomy.

**Trial registration:**

ClinicalTrails.gov, NCT04320979. Registered 25 Match 2020, https://clinicaltrials.gov/ct2/show/NCT04320979

**Supplementary Information:**

The online version contains supplementary material available at 10.1186/s12885-021-08852-y.

## Background

The survival benefits of postmastectomy radiation therapy (PMRT) in axillary node-positive breast cancer have been confirmed by prospective randomized trials and meta-analyses [1–4]. In all these studies, the treatment volume included the chest wall plus comprehensive regional nodal areas. The internal mammary node (IMN) chain is one of the major pathways of lymphatic drainage in breast cancer. Historical surgical series have demonstrated that the incidence of IMN metastasis was 15.5% in patients after extended radical mastectomy [5] and IMN metastasis was more often observed in patients with positive axillary nodes or medial tumors compared with those without [6]. Although the clinical recurrence rate in an untreated IMN region is rare, 1.5% [7], the subclinical disease harbored in these nodes might subsequently metastasize to distant areas without manifesting in the IMN region.

Early randomized trials, conducted in the era before the availability of systemic therapy, showed that IMN dissection did not improve overall survival (OS) [8, 9]. As a result, IMN dissection is abandoned. However, patients with a positive IMN had poorer OS than those with a negative IMN [9]. There is ongoing controversy regarding whether the IMN should be included in the radiation treatment volume, largely because of the unconfirmed survival benefit and the concerns for added risk of cardiac toxicity from IMN irradiation (IMNI). Two large prospective studies evaluating the specific role of IMNI showed conflicting results. A French randomized trial showed no overall survival benefit associated with IMNI in patients with node-positive or high-risk node-negative breast cancer after mastectomy [10]. While a multicenter, population-based, prospective cohort study launched by the Danish Breast Cancer Cooperative Group (DBCG) demonstrated that IMNI increased OS significantly in patients with node-positive breast cancer [11]. It should be noted that the patient populations enrolled in these two studies were different and both studies were conducted before modern systemic treatment was introduced. The OS benefit from IMNI is highly dependent on the efficacy of systemic therapy. It is hypothesized that patients will benefit most from IMNI if systemic therapy is effective to control the distant disease, but not sufficient to sterilize the subclinical disease in the IMN. The other concern for IMNI was that it might increase cardiac mortality and compromise the survival benefit of IMNI [12–14]. Previous studies lacked comprehensive prospective assessment of cardiovascular toxicity and the follow-up was probably too short to show a significant difference in late cardiovascular toxicity. Improvements in radiation techniques, such as computed tomography (CT)-based target delineation, three-dimensional (3D) conformal radiotherapy (RT), and cardiac-sparing techniques [15], have allowed for increased target conformality and minimized heart dose, which might make IMNI safe for most patients.

According to the 2021 National Comprehensive Cancer Network (NCCN) guidelines for breast cancer, IMNI should be considered strongly when delivering regional nodal irradiation (RNI). The absence of strong evidence for or against the IMNI, has resulted in IMNI being performed selectively in real-world clinical practice; however, the optimal subgroups have not yet been identified clearly. The criteria for IMNI in different national guidelines varies, despite the guidelines being based on the same evidence. This has led to the percentages of women studied who might be considered for IMNI in different countries varying substantially, from 13 to 59% [16].

The value of IMNI in the era of modern systemic treatment and radiation techniques is still unclear; therefore, the present study aims to investigate whether IMNI improves disease-free survival (DFS) in high-risk breast cancer with pathological positive axillary nodes (pN+) after mastectomy. In addition, radiation-induced toxicity, especially cardiovascular toxicity, will be evaluated prospectively. This study will provide high-level evidence for elective IMNI for patients with breast cancer. This article was written according to the Standard Protocol Items: Recommendations for Interventional Trials (SPIRIT) guidelines, and the SPIRIT checklist is provided in supplementary material 1.

## Methods/design

### Study design

This is an open label, randomized, multi-center phase III trial for which 1800 participants will be randomized (1:1) to an IMNI group (IMNI) or a no IMN irradiation group (no IMNI).

A flow chart giving an overview of the study design is shown in Fig. 1.

**Fig. 1 Fig1:**
[figure not shown]
Flow chart of the POTENTIAL trial

### Primary endpoint

DFS with events defined as ipsilateral chest wall, axillary, supraclavicular, or internal mammary nodal recurrence, distant metastasis, contralateral invasive breast cancer, or death from any cause.

### Secondary endpoints

The effect of IMNI on overall survival (OS), IMN recurrence, locoregional recurrence (LRR), and distant metastasis (DM); the incidence of contralateral non-invasive breast cancer or other malignant tumors; the incidence of major cardiovascular toxicity or other adverse events; and Quality of life (QoL) will be assessed.

### Inclusion criteria

Female patients aged between 18 and 70 years oldEastern Cooperative Oncology Group (ECOG) scores of 0, 1, or 2Histologically confirmed invasive breast cancerPatients who underwent total mastectomy and axillary dissection (10 or more axillary lymph nodes dissected) with negative marginsPatients who had ≥4 positive axillary lymph nodes; or 1–3 positive axillary lymph nodes and T3–4; or 1–3 positive axillary lymph nodes and T1–2, and score ≥ 3 based on the following high-risk factors: age ≤ 40 years (score 1), primary tumor involving the inner quadrant (score 1), 2–3 positive axillary lymph nodes (score 1), positive lymphovascular invasion (score 1), re-staged based on the eighth cancer staging system (IB-IIA score 1, IIB-IIIA score 2); or ypN+ (positive for lymph node metastases) after neoadjuvant chemotherapyNo supraclavicular or internal mammary nodal metastases based on images before and after systemic therapyNo distant metastasesCould tolerate radiotherapyTreated with chemotherapy (anthracycline and/or taxane-based combined chemotherapy, ≥ six cycles)Anticipated to receive endocrine therapy for 5 years if indicatedAnticipated to receive anti-HER2 (human epidermal growth factor receptor 2) therapy for 1 year if indicatedLeft ventricular ejection fraction (LVEF) ≥ 50% based on an echocardiogramWilling to be followed-upProvided written informed consent

### Exclusion criteria

Simultaneous bilateral breast cancerReceived sentinel lymph node biopsy alone, without axillary dissectionReceived internal mammary node dissection or sentinel node biopsyNo imaging assessment of the internal mammary node before systemic therapyReceived one-stage breast reconstructionSevere cardiac insufficiency; myocardial infarction or uncorrected unstable arrhythmia or uncorrected unstable angina in the last 3 months; pericardial diseaseHad a history of chest wall or supraclavicular radiotherapyHad simultaneous or previous secondary malignancies, except for non-malignant melanoma skin cancer, papillary thyroid / follicular carcinoma, cervical carcinoma in situ, contralateral non-invasive breast cancer

### Randomization

An eligibility checklist must be completed and patient consent obtained before randomization. Eligible patients will be allocated randomly on a 1:1 basis between IMNI and no IMNI, using a computer-generated randomization scheme with a block size of four. Randomization will be stratified by institution, tumor location (medial/central or other quadrants), axillary lymph nodal burden (1–3, 4–9, ≥10 positive nodes), and neoadjuvant therapy (yes, no).

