### Trial status

Recruitment started in May 2020 and is currently ongoing.

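### A single published block size of four, within institution strata of an open-label trial, makes part of the allocation sequence foreseeable and weakens concealment

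*Protocol article*

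**What the plan says.** Four statements in the protocol article bear on this point.

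- **Scheme (Randomization).** Patients are "allocated randomly on a 1:1 basis between IMNI and no IMNI", "using a computer-generated randomization scheme with a block size of four". One size is given, and nothing says that it varies.
- **Strata (Randomization).** "Randomization will be stratified by institution, tumor location (medial/central or other quadrants"; the two further factors are nodal burden in three classes and neoadjuvant therapy (yes or no).
- **Blinding (Study design).** "This is an open label, randomized, multi-center phase III trial".
- **Timing (Trial status).** "Recruitment started in May 2020 and is currently ongoing". The block size therefore became public during accrual.

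One safeguard is stated in the Randomization section: "An eligibility checklist must be completed and patient consent obtained before randomization". The article does not say who holds the list or how an assignment is released, and it does not give the number of institutions.

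**The concern.** Each block of four holds two patients per arm. Blocks run within institution, staff can see which arm each past patient received, and the three patient factors are known to the clinician before randomization. A site can therefore place a candidate in her stratum, count back through its own record and find her position in the current block. The fourth allocation is then always known, and the third is known whenever the first two match.

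The article itself shows why a clinician might have a preference. The Background says that internal mammary irradiation is used selectively in practice and raises concern about cardiac harm. Cardiac risk factors are recorded at baseline. Someone who foresees the next arm could choose whom to approach. Selection of that kind happens before randomization, so an intention-to-treat analysis does not remove it. It could touch both the DFS comparison and the cardiac comparison.

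**Working it through.** The article gives no figure for predictability, so there is none to reproduce. The design count of 414 events does not enter this check.

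**Inputs from the article.** Block size 4 and 1:1 allocation (Randomization); 2 locations × 3 nodal classes × 2 neoadjuvant levels = 12 strata per institution (Randomization); 1800 patients (Study design).

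**Step 1: one complete block.** There are 6 equally likely orders of two and two. An allocation is certain when one arm's two places are already used. The best guess names the arm with more places left.

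| Position | Probability of being certain | Best-guess accuracy |
|---|---|---|
| 1 | 0 | 1/2 |
| 2 | 0 | 2/3 |
| 3 | 1/3 | 2/3 |
| 4 | 1 | 1 |

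Certain share = (0 + 0 + 1/3 + 1)/4 = 1/3. Best-guess accuracy = (1/2 + 2/3 + 2/3 + 1)/4 = 70.8%, against 50% with no information.

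**Step 2: unfinished blocks.** A stratum with n = 4q + r patients has q × 4/3 certain allocations, plus 1/3 if r = 3. Simulating 1800 patients over 12 strata per institution gives the shares below. The number of sites is an assumption. The unequal case also assumes randomly unequal site sizes and stratum shares of 30/70 for location, 30/45/25 for nodes and 35/65 for neoadjuvant therapy.

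| Sites | Mean patients per stratum, 1800/(12 × sites) | Certain, equal sites and strata | Certain, unequal |
|---|---|---|---|
| 5 | 30 | 32% | 32% |
| 10 | 15 | 31% | 31% |
| 20 | 7.5 | 28% | 28% |
| 30 | 5 | 25% | 26% |
| 40 | 3.75 | 22% | 25% |
| 50 | 3 | 19% | 23% |
| 75 | 2 | 13% | 20% |

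In patients this is about 0.32 × 1800 = 576 at 5 sites and 0.28 × 1800 = 504 at 20. At 75 sites it is 0.13 × 1800 = 234 to 0.20 × 1800 = 360.

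**Step 3: can a site wait for a preferred slot?** The planned accrual of 1800 over 5 years is 360 a year. With 20 sites (assumed) there are 240 strata, so 360/240 = 1.5 patients per stratum per year, or one every 8 months. Under the assumed shares the largest stratum holds 0.70 × 0.45 × 0.65 = 20.5% of a site's 18 patients a year. That is 3.7 a year, or one about every 14 weeks. The Radiotherapy section has treatment start within 8 weeks of mastectomy or the end of adjuvant chemotherapy. Holding a patient back until the next slot opens is therefore realistic only at very large centres. Choosing whether to approach her is not limited in this way.

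**Step 4: varied block sizes.** The observer is assumed to know the set of sizes but not the size of each block.

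| Scheme | Certain | Best-guess accuracy |
|---|---|---|
| Fixed 4 | 33.3% | 70.8% |
| Random 4 or 6 | about 5–6% | about 67–69% |
| Random 4, 6 or 8 | about 3% | about 66–68% |

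**The case against.** **A reader might infer that allocation is not concealed at all.** The documents do not support that. The release procedure is not described, and a journal article may leave it to the full protocol. The first two allocations of a block are never certain, and about two thirds or more of all allocations stay uncertain. Foreseeing the rest requires a site to keep a separate record in each of 12 strata. However, central release would not remove the problem, because the prediction comes from past assignments and the published block size. The eligibility checklist and consent before randomization prevent selection after the arm is revealed, but not selective approach beforehand.

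**A reader might also infer a quantified inflation of the DFS type I error.** Suppose 30% of IMNI slots are known, and 20–30% of those go to patients at half the average risk. The spurious hazard ratio would be about 1 − 0.30 × (0.2 to 0.3) × 0.5 = 0.97 to 0.955. At 0.96 and 414 events, the one-sided error is 1 − Φ(1.96 − 0.0408 × √414/2) = 6.1%. Nothing in the documents supports those steering rates, and the direction is a choice. A clinician who believes in IMNI might steer higher-risk women towards it. The mirror-image effect gives 1 − Φ(1.96 + 0.415) = 0.9%, below the planned 2.5%. Nodal burden, tumor location and neoadjuvant therapy are also fixed within a stratum, so steering would have to work through other factors.

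Two further objections stand. The certain share falls below a quarter if there are many small sites, and varied blocks barely hinder someone who acts on a likely rather than a certain allocation.

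**Conclusion.** The weakness is real and moderate. It follows from what the article states: one block size, institution strata, open-label treatment and disclosure during accrual. One third of allocations are certain in complete blocks. Across assumed numbers of sites from 5 to 75 the share is about 32% down to 13–20%. These are upper figures, because they assume perfect tracking by stratum.

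The supported conclusion is that concealment is weakened because part of the sequence is foreseeable. The documents do not show that any site has used this, and they give no basis for the size or sign of a resulting bias in DFS, which could favour either arm. A change is worthwhile because it is cheap and closes a route to bias that the planned analysis cannot correct.

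**What to change.** For all patients still to be randomized:

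1. Keep the four stratification factors, but replace the fixed blocks with centrally generated permuted blocks of randomly varying size, for example 4 and 6, or 4, 6 and 8. Withhold the sizes from sites and public documents. Central minimization with a random element is the alternative, and deserves consideration because varied blocks reduce certainty far more than they reduce guessing accuracy.
2. Record the date of the changeover.
3. Add a sensitivity analysis of DFS by period, before and after the change. It should be read as descriptive, because each period holds only part of the events.

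The cost is reprogramming the randomization system, a short amendment and slightly more possible imbalance within small strata. The sample size and primary analysis are unaffected.

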### Pre-treatment evaluation (baseline)

**History and physical examination**: ECOG status, height and weight, and assessment of breast cancer-related lymphedema and shoulder dysfunction**Blood examination:** blood cell count; serum lipids; myocardial enzymes; thyroid hormone**Image examinations:** mammography, breast ultrasonography or breast magnetic resonance imaging (MRI); contrast-enhanced CT of the neck and thorax; regional nodal ultrasonography; ultrasonography, contrast-enhanced CT or MRI of liver; bone scan or positron emission tomography (PET)/CT (recommended for patients with pN3 disease)**Baseline documentation:** QoL; cardiovascular disease risk factors including being a smoker, obesity (body mass index (BMI) > 28 kg/m^2^); hypotension; diabetes; hyperlipidemia; family history of early onset cardiovascular disease (man < 55 years, woman < 65 years)**Cardiac examination:** Twelve-lead electrocardiogram; echocardiography; coronary CT angiography (if the examination is accessible)

### Radiotherapy

Radiotherapy will be administered within 8 weeks after the mastectomy or the end of adjuvant chemotherapy.

In the experimental group, patients will receive irradiation to the chest wall + supraclavicular/infraclavicular fossa + IMN. Patients in the control group will receive irradiation to the chest wall + supraclavicular/infraclavicular fossa. In both groups, we recommend that the clinical target volume (CTV) of supraclavicular/infraclavicular fossa should encompass part of axilla level II on the same slices. Irradiation of level I axilla is at the discretion of the attending physician, considering the risk of axillary nodal recurrence and treatment-related lymphoedema. The delineation of the CTV of the chest wall, supra/infraclavicular fossa, and IMN (CTVcw, CTVsc, CTVim) is recommended in Table 1. The planning target volume (PTV) will be expanded from the CTV with 0.5 cm margin in all directions, but limited to 0.5 cm beneath the skin surface for PTVsc, PTVim and PTVcw2 (without bolus), and limited to skin surface for PTVcw1 (with bolus).

**Table 1 Tab1:** Suggested CTV delineation

CTV	Cranial	Caudal	Medial	Lateral	Ventral	Dorsal
Chest wall	Caudal edge of the sterno-clavicular joint	Caudal edge of the contralateral breast	Within 1 cm to the midline of the body (guided by palpable/visible signs of free skin flap or the contralateral breast)	Mid-axillary line (guided by palpable/visible signs of free skin flap or the contralateral breast)	Skin surface	Anterior edge of the pectoralis minor muscle; includes the pectoralis major muscle and the interpectoral space
Supraclavicular fossa	Caudal edge of the cricoid cartilage	5 mm below the subclavian vein	Medial edge of the internal jugular vein, excluding the thyroid and the common carotid artery	Medial edge of the trapezius muscle and the pectoralis minor muscle	Posterior surface of the sternocleido mastoid muscle and platysma muscle	Ventral surface of the scalene muscle bundle
Infraclavicular fossa (Axilla level III)	Pectoralis minor muscle inserts on the coracoid process	5 mm caudal to the axillary vein cross medial edge of the pectoralis minor muscle	Medial edge of the collar bone and ribs; lateral edge of the junction of the subclavian and internal jugular veins	Medial edge of the pectoralis minor muscle	Posterior surface of the pectoralis major muscle	Dorsal to the subclavian vein and axillary vein (anterior edge of the ribs)
Axilla level II	Cranial edge of the pectoralis minor muscle	Caudal edge of the pectoralis minor muscle	Medial edge of the pectoralis minor muscle	Lateral edge of the pectoralis minor muscle	Posterior surface of the pectoralis major muscle	5 mm dorsal of the axillary vein, or the ventral edge of the ribs and the intercostal muscle
Axilla level I	Axillary vein cross lateral edge of the pectoralis minor muscle	To the level of rib 4–5	Lateral edge of the pectoralis minor muscle	Medial edge of the latissimus dorsi muscle	5 mm anterior the plane defined by the anterior surface of the pectoralis major muscle and the latissimus dorsi muscle	Anterior surface of the subscapularis muscle
IMN region	5 mm caudal to the subclavian vein, thus connecting to the caudal border of the infraclavicular fossa	Cranial edge of the fourth rib	5 mm medial to IM vessels	5 mm lateral to IM vessels	5 mm anterior to IM vessels, excluding the chest wall	5 mm posterior to IM vessels, excluding the lung

Abbreviations: CTV, clinical target volume; IMN, internal mammary nodal

The prescribed dose is either 50 Gy in 25 fractions over 5 weeks at 2 Gy per daily fraction, or 43.5 Gy in 15 fractions over 3 weeks at 2.9 Gy per daily fraction. CT-based 3D treatment plans are required, including 3D conformal RT, intensity-modulated RT (IMRT), or volumetric modulated arc therapy (VMAT). It is required that 95% of the PTV receives 100% of the prescribed dose, the maximum dose (Dmax) of the PTV < 120% of the prescribed dose, and the PTV receiving ≥110% of the prescribed dose is specified to be < 25%. Electron fields are optional for irradiation of the chest wall and the IMN. When an electron field is used, it is required that 90% of the CTVim or CTVcw receive 90% of the prescribed dose. Chest wall bolus should be used for at least 40–60% of the course of RT. Recommended dose constraints for organs at risk (OARs) are shown in Table 2. Position verification before delivering RT will be performed on a linear accelerator (LINAC) at least once per week with an electronic portal imaging device (EPID) or cone beam computed tomography (CBCT).

**Table 2 Tab2:** Suggested dose constraints of organs at risk

Organs at risk	43.5 Gy in 15 fractions	50 Gy in 25 fractions
Heart (left-sided breast cancer)	Dmean < 8 Gy	Dmean < 10 Gy
	V5 < 45%	V5 < 50%
Heart (right-sided breast cancer)	Dmean < 5 Gy	Dmean < 6 Gy
	V5 < 30%	V5 < 35%
Left anterior descending coronary artery	V40 < 2 0%	V40 < 20%
Right coronary artery	V40 < 20%	V40 < 20%
Ipsilateral lung	Dmean < 15 Gy	Dmean < 15 Gy
	V20 < 30%	V20 < 30%
	V5 < 55%	V5 < 55%
Contralateral lung	V5 < 20%	V5 < 20%
Contralateral breast	Dmean < 5 Gy	Dmean < 5 Gy
Spinal Cord PRV	Dmax < 30 Gy	Dmax < 40 Gy
Esophagus/Ipsilateral Brachial plexus	Dmax < 48 Gy	Dmax < 55 Gy
Ipsilateral shoulder joint	V30 < 30%	V30 < 30%
Thyroid gland	Dmean < 28 Gy	Dmean < 3 0 Gy
Liver (right-sided breast cancer)	V5 < 25%	V5 < 25%
Stomach (left-sided breast cancer)	V 5 < 25%	V5 < 25%
Liver (left-sided breast cancer)	V5 < 10%	V5 < 10%
Stomach (right-sided breast cancer)	V5 < 10%	V5 < 10%

Abbreviations: Dmean, mean dose; Vx, percent volume of the structure receiving x Gy; Dmax, maximal dose

